### 11.1 Data sharing

Approximately one year after publication of the main report of this trial individual de-identified data will be available for sharing with researchers who provide a methodologically sound proposal as judged by the steering committee. To gain access, data requestors will need to sign a data access agreement.

## 12. Insurance

When pre-existing insurance is not available, indemnity to meet the potential legal liability of investigators/collaborating hospitals for harm to participants arising from the conduct of the research will be provided by the REDUSE-trial through the sponsor: Region Skåne. The insurance for each country will be specified in each site agreement before the commencement of patient inclusion at that site.

## 13. Funding

The trial will be funded by non-commercial foundations for medical research. Patient recruitment will not commence until there is sufficient funding to allow for inclusion and follow-up of the proposed sample size.

## 14. Timeline

### 14.1 One year following the start of the project (end of 2024).

Run in period by the end of which more than 10 sites should have received training in follow-up evaluations, received a site initiation visit from monitors and started to include patients.

### 14.2 Two years following the start of the project (end of 2025).

- A total of 600 patients should have been included.
- Sites with more than 10 included patients should have received a monitoring visit.

### 14.3 Three years following the start of the project (end of 2026).

- A total of 1200 patients should have been included by the end of the year
- The interim analysis of the first 400 patients with 90-day outcome data should have been completed.

### 14.4 Four years following the start of the project (end of 2027).

A total of 1850 patients should have been included by the end of the year

[figure not shown]

### 15.2 Steering group

All principal site investigators will be part of the steering group. A representative from the newly formed patient organisation "Sepsisföreningen" will be invited to the management group meetings if/when aspects of the conduct of the trial which are deemed to be of importance from a patient perspective are discussed. Such aspects include any change in the protocol with ethical implications.

**Table 1. Study Schedule**

|                                                         | Study day a |   |   |   |   |                          |    |     |     |
|---------------------------------------------------------|------------------------|---|---|---|---|--------------------------|----|-----|-----|
|                                                         | 1                      | 2 | 3 | 4 | 5 | 6- ICU dis. b | 90 | 180 | 365 |
|                                                         | ENROLMENT       |   |   |   |   |                          |    |     |     |
| Eligibility assessment                                  | x                      |   |   |   |   |                          |    |     |     |
| Informed consent                                        | x                      | x | x | x | x | x                        |    |     |     |
| Randomization                                           | x                      |   |   |   |   |                          |    |     |     |
|                                                         | INTERVENTION    |   |   |   |   |                          |    |     |     |
| Protocolized administration of non-resuscitation fluids | x                      | x | x | x | x | x                        |    |     |     |
|                                                         | ASSESSMENTS     |   |   |   |   |                          |    |     |     |
| Mortality                                               |                        |   |   |   |   |                          | x  | x   | x   |
| Complications                                           | x                      | x | x | x | x | x                        |    |     |     |
| Mechanical ventilation-free days                        |                        |   |   |   |   |                          | x  |     |     |
| Cognitive function                                      |                        |   |   |   |   |                          |    | x   |     |
| Health related quality of life                          |                        |   |   |   |   |                          |    | x   |     |
| Hospital-free days                                      |                        |   |   |   |   |                          | x  |     |     |
| Vasopressor-free days                                   |                        |   |   |   |   |                          | x  | x   |     |
| RRT-free days                                           |                        |   |   |   |   |                          | x  |     |     |
| MAKE                                                    |                        |   |   |   |   |                          | x  |     |     |
| Dose of diuretics                                       |                        |   |   |   | x |                          |    |     |     |
| Glasgow Outcome Scale Extended                          |                        |   |   |   |   |                          |    | x   |     |
| WHO Disability Assessment Schedule                      |                        |   |   |   |   |                          |    | x   |     |
| Modified Fatigue Impact Scale                           |                        |   |   |   |   |                          |    | x   |     |
| Number of days in the ICU                               |                        |   |   |   |   |                          | x  |     |     |
| Hypoglycaemia, Hypernatraemia, Acid-base disturbances   | x                      | x | x | x | x | x                        |    |     |     |
| CVC related complications                               | x                      |   | x |   | x |                          |    |     |     |

a) Day 1 one is defined as the day of inclusion.

b) Intervention will only be administered while the patient is in an REDUSE-ICU. If patient is transferred to a non-REDUSE ICU she/he will be considered as discharged from ICU.

RRT= Renal Replacement therapy; MAKE = Major adverse kidney event; CVC = central venous catheter

## Appendix A. Description of collected data

### During screening

- Initials (Initials starting with the first name. E.g. James Tiberius Kirk = JTK)
- Age (years, calculated from date of birth)
- Sex at birth (F/M)
- Lactate (mmol/L; highest value at any time while the patient is in the ICU and receiving vasopressors)
- Variables related to inclusion criteria
  - o Adult (age  $\geq 18$  years) (yes/no)
  - o Septic shock (yes/no) (while in the ICU but no later than 12 hours after ICU admission, defined as: Confirmed or suspected infection AND Need for vasopressor therapy to maintain mean arterial pressure  $\geq 65$  mmHg despite adequate fluid resuscitation ( $\geq 1$  L resuscitation fluid within the last 12 hours) regardless of whether the need for vasopressor arose in connection with sedation AND Lactate  $> 2$  mmol)
  - o Currently receiving vasopressors (yes/no)
  - o Lactate (Highest value at any time while the patient is in the ICU and receiving vasopressors) (A patient may be included even if lactate is  $\leq 2$  at the time of inclusion as long as all of the following are true: The patient needs vasopressors at inclusion AND The patient has had a lactate  $> 2$  and simultaneous need for vasopressor at any time while in the ICU) (mmol/L or mg/dL)
- Variables related to exclusion criteria
  - o Date and time of ICU admission (dd-mmm-yyyy, hh:mm)
  - o Confirmed or suspected pregnancy (yes/no)
  - o Patient previously included in the REDUSE trial (yes/no)

### Consent information

- Patient informed (Y/N) and date (dd-mmm-yyyy)
- Reason not informed (if N)
- Patient consented (Y/N)
  - Patient granted use of data already collected (Y/N)
- Consent withdrawn (Y/N)
- Date of withdrawal (dd-mmm-yyyy)
- Can the data be used (Y/N)
- Can primary outcome (mortality) be collected (Y/N)

### Background data

- Height (cm; Sites using imperial measurements: Record estimated height in feet and inches)
- Weight at baseline (kg, standardized according to local practice; Record the weight measurement taken closest to time of inclusion; Sites using imperial measurements: Record estimated weight in pounds (lbs))
- Body mass index BMI ( $\text{kg}/\text{cm}^2$ )
- Clinical Frailty Score (Patient's estimated level of fitness/frailty prior to hospital admission; Defined according to: <https://www.dal.ca/sites/gmr/our-tools/clinical-frailty-scale.html>)
- Baseline creatinine [lowest in the 12 months preceding randomization] ( $\mu\text{mol}/\text{L}$ )

- Charlson Comorbidity Index (Charlson et al. J Chronic Dis. 1987; 40: 373-83)
- Type of initial antimicrobial treatment
- Suspected pathogen (If culture was taken, indicate the culture result)
  - o Suspected pathogen sensitive to initial antibiotic treatment (sensitive/intermediate /resistant/not available)
- Hospital admission (dd-mmm-yyyy, hh:mm) (Date and time that the patient was admitted to hospital they were randomised at. If the patient was transferred from another hospital, record the date and time of admission to the hospital where the patient was randomised.)
- Hospital location prior to randomization a) Emergency department, b) Operating room, c) Other ICU, d) Other unit
- Steroid treatment prior to hospital admission (Y/N)
- Surgery prior to inclusion/randomization (Y/N), if yes, specify: a) Head and neck, b) Thorax, c) Abdominal/pelvic, d) Extremities, e) Trauma f) Other
- Origin of sepsis (Mellhammar et al. Crit Care Exp 2022; 4: e0697)

Baseline variables at study inclusion (values closest in time to enrolment, within  $\pm 6$  h, unless other timeframe is specified; lab values either arterial or venous.)

- Body temperature (degrees Celsius)
- SAPS-III (Simplified acute physiology score-III) (Moreno et al. Intensive Care Med. 2005;31:1345-55)
- Glasgow Coma Score (GCS) (Teasdale and Jennett B. Lancet. 1974; 2: 81-4)
- Creatinine ( $\mu\text{mol/L}$ )
- Renal replacement therapy (Y/N)
- Bilirubin ( $\mu\text{mol/L}$ )
- Platelet count ( $\times 10^9/\text{ml}$ )
- Mean arterial pressure (mmHg)
- Systolic pressure (mmHg)
- Type of inotropic drug or vasopressor (any dose of dobutamine, dopamine, vasopressin or other V1A agonists, levosimendan, angiotensin II, noradrenaline, adrenaline, milrinone, or other)
- Noradrenaline dose (highest dose in the 6 hours prior to enrollment;  $\mu\text{g/kg/min}$ )
- Corticosteroid treatment (Y/N)
- Atrial fibrillation/flutter (Y/N)
- Ischemic events (Y/N) (criteria described above), if yes, specify: a) Limb, b) Cerebral, c) Heart, d) Intestine
- Heart rate (bpm)
- Ventilatory support (nasal catheter, nasal high flow oxygen, Hudson mask or similar, reservoir mask, non-invasive mechanical ventilation, invasive mechanical ventilation [defined as mechanical ventilation through an orotracheal tube or through a tracheostomy], none. Classification at each day will be based on the highest level of support,
- CRP (g/L)
- Leucocytes ( $\times 10^9$  cells/L)
- Haemoglobin (g/L)
- Potassium (mmol/L)

- Sodium (mmol/L)
- Chloride (mmol/L)
- Blood glucose (mmol/L)
- Arterial blood gas on inclusion (Y/N)
- FiO2 (%)
- PaO2 (kPa)
- PaCO2 (kPa)
- pH
- Base excess (BE, mEq/L)
- Volume of fluid intake in the 24h prior to inclusion (Crystalloids (Ringer's acetate/lactate [ml], 0.9% NaCl [ml], other [ml]); Colloids (Albumin 4-5% [ml], Albumin 20% [ml], other [ml]); Blood products (Erythrocytes [ml], Plasma [ml]- Platelets [ml]); Glucose (any concentration [ml]); Parenteral nutrition (ml); Enteral nutrition (ml); Enteral water (ml))

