#### 5.2 Intervention

Participants will receive non-resuscitation fluids according to the protocol described below within two hours of randomization. Non-resuscitation fluids are defined as fluids other than colloids, blood products, or crystalloids administered to correct hemodynamic impairment as noted in the participants' charts. The type of maintenance fluids will be given according to usual care at each respective centre with the objective to use similar types of fluids in both groups. The allocated treatment will be continued while the participant is admitted in an ICU participating in the REDUSE trial up to a maximum of 90 days. Patients readmitted to an ICU

participating in the REDUSE trial within 90 days of inclusion will receive the same treatment to which they were initially allocated regardless of admission diagnosis.

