#### 5.4 Blinding

The clinical team caring for participants bedside and the research staff collection data up to 90 days after inclusion will not be blinded due to the nature of the intervention. The participants and their family will not be informed about group allocation. The steering group, author group, trial statisticians, outcome assessors at 6 months and at one year, the trial coordinating team, manuscript writers and the data safety and monitoring committee will be blinded to group allocation. The two groups will be coded as "A" and "B". Two conclusions from all outcomes in the main manuscript will be drawn: one assuming "A" is the intervention group and "B" is the control group - and one assuming the opposite. All conclusions must be approved by the author group before the code is broken.

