## 10. Statistical analysis plan

A detailed statistical analysis plan will be published before the randomization of the last participant. In short, data will be analysed by two independent statisticians blinded to the treatment on an intention-to-treat basis. The intention-to-treat population is defined as all randomized patients who consented to use of their data. The per-protocol population is defined as all randomized patients fulfilling all inclusion criteria and no exclusion criteria who consented to use of their data, and excluding those having one or more protocol deviations as defined above (5.5.3). Patients will be considered to be included in the trial when they are randomized.

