## 10.4 Subgroup analysis

The heterogeneity of the intervention effect on the primary and secondary outcomes will be assessed in subgroups based on baseline characteristics at randomization.

- Mechanical ventilatory support at the time of randomization (defined as invasive or non-invasive mechanical ventilation or nasal high flow treatment [yes/ no]).
- Acute kidney injury at the time of randomization ( $\geq$  KDIGO stage 1 [yes/ no])
- Sex (male/ female)
- Age ( $\geq$  65 years [yes/ no])
- Frailty Clinical frailty scale ( $\leq$  3, 4,  $>$ 4).
- Weight at admission ( $\geq$  median of the intention to treat population [yes/ no])
- Validated infection as suggested by a Linder-Mellhammar score  $\geq$  3 (yes/ no) (Mellhammar 2022)
- IV fluid at time of randomization  $<$  30 ml/kg (yes/ no)

- Plasma Lactate ( $> 4$  mmol/l) (yes / no)

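### Appendix A lets baseline creatinine and weight be measured after randomisation, although subgroups and new-onset kidney events depend on status at randomisation

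*Protocol*

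**What the plan says.** **Baseline window.** The baseline list in Appendix A is introduced as "Baseline variables at study inclusion (values closest in time to enrolment, within" plus or minus 6 h, "unless other timeframe is specified; lab values either arterial or venous". It contains creatinine, renal replacement therapy (RRT), ventilatory support and ischaemic events. The ventilatory support item adds: "Classification at each day will be based on the highest level of support".

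**Weight.** Under Background data, weight has its own rule: "Record the weight measurement taken closest to time of inclusion". No limit is set on either side of inclusion.

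**Time zero and treatment.** Section 10: "Patients will be considered to be included in the trial when they are randomized". Section 5.2: "Participants will receive non-resuscitation fluids according to the protocol described below within two hours of randomization". Section 5.4: "The clinical team caring for participants bedside and the research staff collection data up to 90 days after inclusion will not be blinded".

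**Use of the values.** Section 10.4 says that effect heterogeneity "will be assessed in subgroups based on baseline characteristics at randomization". It repeats the time point for ventilatory support and for AKI, and it lists weight at admission as a further subgroup variable. Section 3.2 counts stage 3 AKI as a complication only if it is of new onset, and the kidney composite (MAKE) in section 3.3 includes newly started RRT. Under section 5.5.1, Day 1 begins at randomisation.

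**The concern.** A subgroup variable should be fixed before treatment can act on it. If it is measured afterwards, patients may move between strata for reasons connected with their arm, and the comparison within a stratum is no longer fully protected by randomisation. In the same way, a new event can only be recognised against a known status at time zero. A baseline field that may be filled from the first hours of follow-up leaves that status uncertain. Here the treatment acts on fluid volume, and it is open-label for bedside staff and for those who collect data up to day 90.

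At stake are the AKI, weight and possibly ventilation subgroups, and the new-onset condition in one component of the complications outcome and one component of MAKE.

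**Working it through.** The protocol states no figure to reproduce here. The check is interval arithmetic, then a field-by-field comparison, then an illustration on assumed inputs.

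**1. Time axis, with randomisation at 0 h**
- Baseline window: -6 h to +6 h, length 12 h (Appendix A).
- Part after randomisation: 6 h; 6/12 = 50%.
- Treatment start: between 0 and 2 h (section 5.2).
- Part under allocated treatment: 6 - 2 = 4 h if treatment starts at the limit (4/12 = 33%), and 6 h if it starts at once (50%).
- Day 1 recording starts at 0 h (section 5.5.1), so 0 to 6 h is both baseline and follow-up.

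These are shares of the window. They are not shares of the values, because the value nearest to enrolment is taken.

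**2. The nine subgroup variables in section 10.4 against their fields in Appendix A**
- *AKI*: the baseline list has no separate AKI item, so status must be derived from inclusion creatinine and RRT, both under the plus or minus 6 h rule. Exposed.
- *Weight*: nearest to inclusion, without limit. Exposed. Section 2.4 reports a median reduction in administered fluid of 3.6 L over the first 3 days in the feasibility trial, so a late first weight could carry a treatment effect.
- *Ventilatory support*: under the window. Support is a continuous state, so the nearest status should be that at randomisation. However, the highest-level wording, if applied to the inclusion day, would pick up an escalation after randomisation. Less clearly exposed.
- *Prior intravenous fluid*: limited to the 24 h before inclusion. Protected.
- *Lactate*: a screening field, outside this window.
- *Age, sex, frailty, validated infection*: not governed by this window.

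**3. New events**
- The reference creatinine is the lowest in the 12 months before randomisation, so it is protected. What remains open is whether stage 3 AKI or RRT was already present at 0 h.
- Creatinine drawn at, say, +3 h can serve as the inclusion value while the same hour belongs to Day 1. No rule says which record decides.

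**4. Precedent within Appendix A.** Noradrenaline dose is limited to the 6 h before enrolment. With reference creatinine and prior fluid, that makes three items already restricted to the time before randomisation.

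**5. Illustration of size (all inputs assumed except the 45% overall mortality from section 10.1.1).** Take no true effect, half of the patients in each stratum, and mortality of 55% (yes) and 35% (no), which averages 45%. In one arm only, a fraction q of the no stratum, with 45% mortality, is recorded as yes.
- Yes stratum: (0.5 × 0.55 + 0.5q × 0.45) / (0.5 + 0.5q)
- No stratum: (0.5 × 0.35 - 0.5q × 0.45) / (0.5 - 0.5q)

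| q | Mortality yes | OR yes | Mortality no | OR no | Ratio of ORs |
|---|---|---|---|---|---|
| 2% | 54.8% | 0.992 | 34.8% | 0.991 | 1.001 |
| 5% | 54.5% | 0.981 | 34.5% | 0.977 | 1.004 |
| 10% | 54.1% | 0.964 | 33.9% | 0.952 | 1.013 |

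Odds ratios are against the undisturbed arm. Both strata show a spurious benefit although the overall odds ratio is 1, while the interaction hardly moves. The shift in one arm only is an unfavourable assumption.

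**The case against.** The strongest reply is that the 6 h window yields where another timeframe is given, and that section 10.4 gives one for ventilatory support and AKI. That is a fair reading of the intention, but Appendix A does not refer to section 10.4. The appendix governs what is entered: if the entered creatinine is a later one, the label in the analysis section does not change it. Nor does the reply settle weight, which section 10.4 ties to admission and Appendix A ties to inclusion.

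It may also be said that a statistical analysis plan can define baseline. It can, but Appendix A lists no sampling times for these items. If none are captured, later values cannot be separated without going back to source records.

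Two stronger readings are tempting and are not supported:
- *That ischaemic events vanish from the complications outcome.* Section 3.2 requires new onset only for severe AKI. The ischaemic items count as events in the ICU, nothing subtracts events flagged at baseline, and the daily record runs from randomisation. The issue is a period that belongs to two records, not a demonstrated loss.
- *That unblinded staff choose which value to record.* For laboratory values the nearest-in-time rule leaves little choice, and source data verification and central monitoring are planned (sections 6.1 and 8.2).

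The objection also stands in that many nearest values will precede randomisation, and that a few hours of altered fluid volume may change creatinine little.

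**Conclusion.** The point holds within limits. As written, AKI status derived from creatinine, and weight, can be post-randomisation values; ventilatory support can be too if the highest-level wording is applied to the inclusion day. The time-zero status behind new-onset stage 3 AKI and new RRT is not pinned down.

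The size is unknown. The window arithmetic (6 h after randomisation, 4 to 6 h under treatment) is firm, but a reader might go on to infer that a sizeable fraction of the planned 1850 patients sits in the wrong subgroup. The documents give no rate of class change, and the nearest-value rule means that a change within 6 h is often not the value recorded. The affected share is probably small. In the illustration, even a 10% shift in one arm moves the stratum odds ratios only to 0.95-0.96.

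The 90-day mortality comparison in all randomised patients does not use these fields. Section 10.2 declares secondary and explorative results hypothesis generating. This is a cheap correction worth making, not a threat to the main conclusion.

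**What to change.** - For the subgroup variables (creatinine and AKI status, ventilatory support, weight) and the flags for events already present (RRT, AKI stage, ischaemic events), define baseline as the last value or status at or before randomisation.
- Do not use later values for subgroup membership or prevalent status; leave the item missing instead. Purely descriptive baseline items may keep the present window.
- State that any qualifying event that starts after randomisation counts as an outcome, whichever form it was entered on.
- Say that the highest-level rule for ventilatory support applies to the daily records and not to the baseline item.
- Reconcile section 10.4 with Appendix A, including whether the weight subgroup refers to admission or to inclusion.

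The cost is revised data-entry guidance, a query on values already entered with a later time, and slightly more missing baseline values, mainly in patients with no earlier measurement. The sample size does not change. The overlap of these fields with the period after randomisation falls to zero: from 6 h for the items in the window, and from an unlimited period for weight.
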